## Abstract

**Background:**

A single injection of local anaesthetic (LA) in the erector spinae plane block (ESPB) can reduce pain after modified radical mastectomy (MRM) surgery, but the duration of analgesia is affected by the duration of the LA. The aim of this study is to investigate the effect of continuous ESPB on acute and chronic pain and inflammatory response after MRM surgery.

**Methods:**

In this prospective, randomised, controlled trial, we will recruit 160 patients, aged 18–80 years, scheduled for elective MRM surgery under general anaesthesia. They will be randomly assigned to two groups: a continuous ESPB group (group E) and a sham block group (group C). Both groups of patients will have a nerve block (group C pretended to puncture) and an indwelling catheter fixed prior to surgery. Electronic pumps containing LA are shielded. The primary outcome is the total consumption of analgesic agents. The secondary outcomes include the levels of inflammation-related cytokines; the occurrence of chronic pain (post-mastectomy pain syndrome, PMPS); static and dynamic pain scores at 2, 6, 12, 24 and 48 h postoperatively; and post-operative and post-puncture adverse reactions.

**Discussion:**

Analgesia after MRM surgery is important and chronic pain can develop when acute pain is prolonged, but the analgesic effect of a nerve block with a single injection of LA is limited by the duration of drug action. The aim of this trial is to investigate whether continuous ESPB can reduce acute pain after MRM surgery and reduce the incidence of chronic pain (PMPS), with fewer postoperative analgesic drug-related complications and less inflammatory response. Continuous ESPB and up to 12 months of follow-up are two innovations of this trial.

**Trial registration:**

Chinese Clinical Trial Registry (https://www.chictr.org.cn/) ChiCTR2200061935. Registered on 11 July 2022. This trial is a prospective registry with the following registry names: Effect of ultrasound-guided continuous erector spinae plane block on postoperative pain and inflammatory response in patients undergoing modified radical mastectomy for breast cancer.

**Supplementary Information:**

The online version contains supplementary material available at 10.1186/s13063-023-07777-0.

## Introduction

### Background and rationale {6a}

Breast cancer is the leading cause of cancer-related deaths among women worldwide, with a standardised incidence rate of 47.8 per 100,000 and a standardised mortality rate of 13.6 per 100,000 in 2020 [1]. The current treatment of choice for breast cancer is surgery, and modified radical mastectomy (MRM) surgery remains the most common surgical treatment modality [2]. MRM surgery involves the breast and axillary region, with large surgical incisions, and is prone to acute and chronic post-operative pain, which is one of the main factors causing stress and inflammatory reactions. Now, “post mastectomy pain syndrome” (PMPS) has become the main term to represent chronic pain persisting for at least 3 months after breast cancer-related surgery; the incidence of PMPS can range from 25 to 60% [3]. Patients with PMPS consume significantly more intraoperative or postoperative intravenous and oral analgesic medication and have more severe acute postoperative pain [3, 4]. Therefore, perioperative complex regional nerve blocks, implementation of multimodal analgesia, reduction of intravenous and oral analgesic drug consumption and enhanced acute pain management have positive significance in preventing PMPS, reducing the incidence of perioperative complications, alleviating stress and inflammatory responses and improving prognosis.

Regional analgesia techniques have been widely accepted by anaesthetists as the basis for multimodal analgesia. The erector spinae plane block (ESPB) is a novel regional block technique that was first reported in 2016 by Forero et al. [5] to be successfully applied to the treatment of thoracic neuropathic pain with good efficacy. Studies have shown that injecting 20 ml of 0.5% ropivacaine into the deep surface of the erector spinae fascia at the level of the T5 transverse process blocks the spinal nerve running there and blocks the ipsilateral T3-T9 spinal innervation area [5, 6]. A number of studies have shown good postoperative analgesia with ESPB in MRM surgery [7–9]. However, most current studies were conducted with a single injection of local anaesthetic (LA), and the duration of analgesia was limited by the duration of the LA. The perforator interface of the ESPB is free of important blood vessels and organs, and ultrasound-guided indwelling catheters for continuous ESPB are feasible. Therefore, we designed this trial to investigate the effect of ultrasound-guided continuous ESPB on postoperative pain and inflammatory response in patients undergoing MRM surgery for breast cancer. It is anticipated that continuous injection of LA to prolong the duration of analgesia will reduce the degree of acute post-operative pain and the incidence of chronic pain and decrease the degree of inflammatory response by continuously blocking the transmission of injurious stimuli.

## Objectives {7}

We hypothesised that ultrasound-guided continuous ESPB would reduce the amount of analgesic medication used during and after surgery and reduce the level of pain during catheter retention, thereby reducing the short-term side effects associated with anaesthesia and decreasing the incidence of post-surgical inflammatory reactions and chronic pain. To test this hypothesis, two groups of patients undergoing MRM surgery will be compared: group E received a continuous ESPB and group C received a sham puncture. The main aim of this study is to test the hypothesis that continuous nerve block overcomes the temporal limitations of a single injection of drug and provides longer analgesia, thereby reducing analgesic drug consumption, inflammatory response and the incidence of PMPS.

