### Interventions

#### Explanation for the choice of comparators {6b}

We describe all interventions as receiving continuous ESPB combined with general anaesthesia in full during the signing of the informed consent form. A sham nerve block is used for the comparator. In group C, only the erector spinae muscle is scanned with an ultrasound probe, followed by fixation of the line for the injection of the drug in the back and placement of the same electronic drug injection pump as in group E. In all patients, the electronic drug injection pump is wrapped in a black bag and kept for 48 h. The risks of ropivacaine infusion and systemic toxicity will be communicated to patients during the informed consent interview.

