##### Description for Intervention

Eligible participants will be randomly allocated in equal proportions between the two groups mentioned above to receive nerve block in the surgical preparation room. Each patient will receive 5 µg of sufentanil intravenously before nerve block. Participants will be placed in the lateral position, routinely disinfected and placed on the ultrasound probe using a sterile protective sleeve. All operations will be performed using a high-frequency line array probe on an M-Turbo ultrasound machine (SonoSite Inc., USA) and a short bevel puncture needle [Contiplex D continuous plexus block kit (B. Braun, Germany), 400 mm]. All patients will use 2 mL of 2% lidocaine for skin infiltration anaesthesia, explaining to the control group patients that this is nerve block puncture pain, and blinding the control group patients accordingly. Disinfect the skin and apply a towel, wrap the ultrasound probe in a sterile bag. Under ultrasound guidance, search for the erector spinae muscle, rhomboid muscle and trapezius muscle at the T4–T5 level, and insert the needle 3 cm next to the spinous process of the T5 thoracic vertebrae. Use in-plane needle insertion technology, and confirm under ultrasound that the end of the needle is located in the deep surface of the erector spinae muscle, and the puncture is successful. Based on previous literature and pre-experiments, we will select 0.5% ropivacaine 25 mL for the ESPB at the T4–T5 level and then use an indwelling catheter (depth 5 cm) and an electronic drug injection pump set at 0.2% ropivacaine 5 ml/h for continuous infusion [9]. All patients will be observed for 30 min after completion of the block, and the level of sensory block is measured and recorded every 5 min by another anaesthetist who is unaware of the group. Patients in group E who do not experience hypoalgesia during the observation period will be considered block failures and will be excluded at the time of final data unblinding. Patients in both groups will be given patient-controlled intravenous analgesia (PCIA) until 48 h after surgery. The PCIA protocol is as follows: sufentanil 100 µg + granisetron 6 mg + normal saline diluted to 100 ml, background dose 1.5 ml/h, self-controlled single dose 1.5 ml/time, locking time 30 min. If the static VAS score is ≥ 4, then parecoxib sodium 40 mg intravenous injection will be administered for rescue analgesia.

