Although ESPB was used with definite effectiveness for post-surgical analgesia, most clinical applications were currently for a single injection of LA [7–9]. Theoretically, the maximum duration of a single dose of LA is 12 h [21]. In contrast, continuous administration of the LA after placement of the catheter can provide a longer duration of analgesia. A multicentre, high-quality RCT showed that nerve block with a single injection of LA improved acute pain after breast cancer surgery but did not reduce the incidence of chronic pain [22]. There are still few studies on the use of continuous ESPB in analgesia for MRM surgery, and our research on this occasion is much needed.

Poorly controlled acute pain after surgery is an important contributor to chronic pain and stress and inflammatory responses [23]. We believe that improving acute pain within 48 h of surgery is even more important and therefore used it as the primary outcome for this study. We also evaluated the postoperative recovery in a multidimensional manner by comparing the incidence of PMPS, the QoR-15 score, the concentration of perioperative inflammatory cytokines, total consumption of analgesic agents and post-surgical adverse effects.

In summary, our single-centre, prospective, double-blind RCT will reveal the effect of continuous ESPB on postoperative pain and inflammatory response in patients undergoing MRM surgery and is expected to provide a strong scientific basis for its use in the management of MRM surgery postoperatively. Continuous ESPB and up to 12 months of follow-up are two innovations of this trial. In addition, our results may be extrapolated to other chest procedures and comparisons with the application of different concentrations of local anaesthetics.

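### The sentence stating the main aim (continuous block overcomes the limits of a single injection) does not match a design that compares bolus plus infusion with sham only

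*Protocol article*

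**What the plan says.** Objectives {7} makes two statements about purpose. The first is a hypothesis that continuous ESPB lowers analgesic use and pain, with downstream benefits. It is to be tested by comparing two groups: "group E received a continuous ESPB and group C received a sham puncture". The section then closes with a different claim, giving the main aim as testing that "continuous nerve block overcomes the temporal limitations of a single injection of drug and provides longer analgesia".

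The arms are described consistently elsewhere. The abstract lists "a continuous ESPB group (group E) and a sham block group (group C"). Under Description for Intervention, group E gets both components: "we will select 0.5% ropivacaine 25 mL for the ESPB at the T4–T5 level and then use an indwelling catheter" and a pump for continuous infusion. For the comparator, Explanation for the choice of comparators {6b} says "In group C, only the erector spinae muscle is scanned with an ultrasound probe", after which a line and an identical pump are fixed in place.

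The primary outcome is one cumulative patient-controlled analgesia (PCA) total. Intravenous PCA runs to 48 h after surgery. Pain on a visual analogue scale (VAS) at 2, 6, 12, 24 and 48 h is secondary. Section {20b} plans no additional analyses. On how long one injection lasts, the Discussion says: "Theoretically, the maximum duration of a single dose of LA is 12 h".

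**The concern.** The closing sentence of Objectives {7} names a contrast between continuous block and single injection, but no such contrast is randomised. The protocol itself gives reason to expect a benefit over sham from the bolus alone. The Background reports good analgesia with ESPB in this operation, mostly from single-injection studies. The Discussion cites a multicentre trial in which a single-injection nerve block improved acute pain after breast cancer surgery. A positive result against sham is therefore plausible even if the infusion adds nothing.

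What is at stake is what a positive trial may be said to show. With the aim as written, a lower PCA total in group E could be reported as confirming that a catheter and infusion improve on one injection. The data would not support that.

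**Working it through.** **1. What the comparison estimates.** Write the expected outcome under bolus plus infusion as m(BI), under bolus alone as m(B), and under sham as m(S). The trial estimates

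m(BI) − m(S) = [m(BI) − m(B)] + [m(B) − m(S)].

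The main-aim sentence concerns the first bracket. The planned numbers are 80 on BI, 80 on S and 0 on B, so m(B) has no data and neither bracket can be estimated from the randomised comparison. The left side can be non-zero when the first bracket is exactly zero. More patients in the existing two arms would not change this.

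**2. Does the timing of outcomes separate the two?** The primary outcome is a single total and gives no resolution in time. VAS is resolved in time, and the same identity holds at each time point. A late difference from sham isolates the infusion only if m(B) = m(S) at that time, that is, if the bolus has no remaining effect. The 12 h figure in the Discussion makes this plausible at 24 and 48 h, but it is a theoretical maximum taken from outside the trial. Sample size {14} adds a further caution: it plans on a 48 h dynamic VAS difference of 4.2 − 3.6 = 0.6 for a cited ESPB group, without saying whether that group had a single injection or a continuous block. If it was a single injection, a 0.6-point difference at 48 h would be expected with no infusion at all.

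**3. The sample size.** Inputs from Sample size {14} and Statistical methods {20a}: SDs 1.4 and 1.1, difference 0.6, two-sided alpha 0.05, power 80%, dropout 11%.

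- Root-mean-square SD = √[(1.4² + 1.1²)/2] = √1.585 = 1.259.
- Normal approximation: n = 2 × (1.960 + 0.842)² × 1.585 / 0.6², which rounds up to 70 per group.
- Noncentral t: power is just under 0.800 at 70 and 0.805 at 71, so 71 per group, as stated.
- Dropout: 71 / 0.89 = 79.8, so 80 per group, as stated.

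The stated figures reproduce. They size ESPB against control, so rewording the aim to that contrast leaves them unchanged.

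**4. What testing the sentence as written would need (illustration only).** The documents give no effect of continuous over single-injection ESPB. Assume a single-injection arm, SD 1.259, and an incremental effect equal to a share of the 0.6-point planning difference (normal approximation):

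| Share of 0.6 | Difference | n per arm | With 11% dropout | Power at 71 per arm |
|---|---|---|---|---|
| 100% | 0.60 | 70 | 79 | 0.81 |
| 75% | 0.45 | 123 | 139 | 0.57 |
| 50% | 0.30 | 277 | 312 | 0.29 |
| 25% | 0.15 | 1106 | 1243 | 0.11 |

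Unless the infusion adds as much over a bolus as ESPB adds over control in the planning data, an extra arm of the present size would be underpowered.

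**The case against.** The strongest reply is that one sentence is at fault, not the trial. Objectives {7} first states a hypothesis that a sham control does test, and both the abstract and the closing summary of the Discussion speak of the effect of continuous ESPB, not of superiority to single injection. That stands. A reader might infer from the mismatch that the trial cannot answer its main question or that sham is the wrong comparator. The documents do not support either inference.

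It can also be said that the design is not silent on persistence, because VAS at 24 and 48 h is already planned beyond the stated 12 h. That stands too, as indirect evidence against an outside benchmark. The same applies to chronic pain. The Discussion cites a trial in which a single-injection block did not reduce its incidence, but setting a benefit here against that result would be a comparison across trials.

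A reader might also divide 12 h by 48 h and say that the bolus accounts for a quarter of the primary outcome. The documents do not support that figure. The block is placed before surgery, so fewer than 12 of its hours fall after the operation. A share of time is also not a share of effect: the PCA background rate is 1.5 ml/h in both groups, so any bolus effect acts through the demand doses.

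Finally, the Discussion suggests that "our results may be extrapolated to other chest procedures and comparisons with the application of different concentrations of local anaesthetics". This goes beyond the one regimen and one operation studied, but it is hedged and is not part of the aim. It adds little weight here.

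**Conclusion.** The sentence is wrong as written: no randomised contrast in this trial can test whether continuous block overcomes the limits of a single injection. The extent is definite, with zero of 160 participants in a bolus-only arm, but the reach is narrow. The continuous-ESPB-versus-sham hypothesis, the primary comparison and the 71 (80 after dropout) per group are unaffected. No size can be put on the bolus share of any difference, because the documents give no figure for it. The conclusion rests only on the protocol's own description of the arms, which is consistent throughout. It does not depend on the 12 h figure or on the illustration of a third arm.

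**What to change.** Reword the last sentence of Objectives {7} so that the main aim is the effect of continuous ESPB, meaning bolus plus infusion, compared with sham block on analgesic consumption, inflammatory response and chronic pain. State there, and in the eventual report, that the trial does not test continuous against single-injection ESPB, and limit the conclusions accordingly.

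The planned VAS at 24 and 48 h may be presented as indirect, supportive evidence that analgesia persists beyond the stated duration of one dose. PCA consumption after 12 h could be added on the same footing where pump readings exist, but this is optional. The 12 h is theoretical, early relief may carry over into later demand, section {18a} has the postoperative form completed at 48 h and at discharge, and recruitment has already begun, so 12 h readings may be missing for enrolled patients.

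The cost is a narrower claim and a wording amendment, which section {25} requires the Ethics Committee to approve. Arms, treatment, analysis and sample size stay as they are.

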## Trial design {8}

This study will be conducted as a prospective, single-centre, double-blind, parallel-group, randomised, controlled trial.

## Methods: participants, interventions and outcomes

### Study setting {9}

The study will be conducted in patients undergoing elective MRM surgery for breast cancer in Huzhou Central Hospital, Zhejiang, China.

### Eligibility criteria {10}

The inclusion and exclusion criteria for participants in this study are as follows:

Inclusion criteria:Scheduled to undergo the elective MRM surgery for breast cancer under general anaesthesiaAmerican Society of Anesthesiologists (ASA) score of Ito IIIFemale aged 18–80 years with capacityAgree to participate in this study and sign informed consent

Exclusion criteria:Long-term use of opioids or other analgesicsKnown hypersensitivity to the study medication (ropivacaine)Severe mental illness and difficulty communicatingLiver or renal insufficiencyWithout informed consentHistory of breast surgery

### Who will take informed consent? {26a}

The eligibility of participants will be determined jointly by the anaesthesia and breast surgeons of the study team at our hospital. Written informed consent will be obtained from each study participant 1 day prior to surgery to allow sufficient time for participants to consider and voluntarily choose to participate in this study.

### Additional consent provisions for collection and use of participant data and biological specimens {26b}

Prior to obtaining informed consent from the participant, we will explain the method of puncture for the continuous ESPB and describe the pre-, intra- and post-operative data and venous blood that need to be asked for and collected. The details of what needs to be asked and collected will also be listed in the informed consent form. We will collect 3 ml of venous blood at a predetermined time point for plasma inflammatory cytokine and ropivacaine concentration assay. The blood sample will be sent to the central laboratory of our hospital. After centrifugation, the serum will be stored in test tubes at − 80 °C. Plasma levels of the inflammatory markers tumour necrosis factor (TNF)-α, interleukin (IL)-6 and IL-10 will be quantified using commercial enzyme-linked-immunosorbent serologic assay (ELISA) kits. Use high-performance liquid chromatography to determine the plasma concentration of ropivacaine.

### Interventions

#### Explanation for the choice of comparators {6b}

We describe all interventions as receiving continuous ESPB combined with general anaesthesia in full during the signing of the informed consent form. A sham nerve block is used for the comparator. In group C, only the erector spinae muscle is scanned with an ultrasound probe, followed by fixation of the line for the injection of the drug in the back and placement of the same electronic drug injection pump as in group E. In all patients, the electronic drug injection pump is wrapped in a black bag and kept for 48 h. The risks of ropivacaine infusion and systemic toxicity will be communicated to patients during the informed consent interview.

#### Intervention description {11a}

##### Preparing

All participants are routinely fasted for 8 h prior to the procedure and wait in the surgical preparation room for the nerve block operation while receiving oxygen and monitoring a 5-lead ECG, non-invasive arterial blood pressure and transcutaneous oxygen saturation monitoring. The risk of postoperative nausea and vomiting (PONV) will be assessed using a Koivuranta score, which included five risk predictors: female gender, history of PONV/motion sickness, non-smoker, anticipated postoperative opioid use and surgical time greater than 60 min [9]. Each risk predictor is scored 1 point, with a score of 0–1 as low risk, 2–3 as medium risk and 4–5 as high risk. The risk level of PONV will be recorded. Granisetron 3 mg will be used for single-drug prophylaxis in low-risk patients, and granisetron 3 mg plus dexamethasone 4 mg will be used for combination prophylaxis in middle-high-risk patients.

##### Grouping

The groupings will be numbered sequentially and sealed in opaque envelopes by an independent person not involved in this study. Once participants are in the surgical preparation room, the appropriate serially numbered envelope will be opened by a trained operating room nurse not involved in the study to identify the grouping and the nerve block will be completed according to the grouping. Another researcher who is unaware of the grouping will measure the extent of the nerve block and record relevant data.

